#### Administrative health data

In partnership with TASO and community health clinics, health records will be used to assess clinical outcomes, including HIV status, date of confirmed diagnosis, time of ART initiation, viral suppression, and comorbid medical conditions. Data will be anonymized by sharing the unique Study ID file (linked to identifiers) with TASO, then receiving in return, data linked with the study ID stripped of all identifiers. These data will be linked by study ID within our de-identified dataset and remain confidential and anonymous. All data will be securely stored on a password-protected cloud-based platform, with access limited to approved members of the research team.

### Data analysis

#### Analysis of formative interviews

Interviews will be audio-recorded in Luo, transcribed, and translated in English. Transcription and translation will be conducted by local translators. Back-translation from English to Luo will be used to verify the accuracy of the original translation for 5–8 transcripts in order to enhance the trustworthiness of the findings [36, 37]. Final English transcripts and field notes will be imported into NVivo™ for analysis.

The Framework Method [38] will be used to analyze qualitative data. Researchers will begin by familiarizing themselves with the data by reading transcripts. The analytical process will begin with deductive coding guided by Stangl et al.’s [22] Health Stigma and Discrimination framework, followed by inductive coding for data that does not fit within the framework. Two researchers will independently code a subset of interviews, with a consensus code negotiated through peer-debriefing and coding comparisons undertaken in NVivo™. Agreed codes will be categorized to form an analytical framework which will be applied by researchers to code all subsequent interviews. Once all interviews are coded, data will be summarized using a matrix to facilitate interpretation and the generation of themes within the data [38]. Memos will be drafted throughout data analysis to record methodological decisions and analytical insights.

Descriptive and analytical strategies will be used to enhance rigor throughout qualitative data collection and analysis. The research team will maintain an audit trail of analytical steps and decisions taken throughout the research process. Peer-debriefing between researchers and members of the research team will enhance the trustworthiness and credibility of the findings. Member checking of findings [39] will occur within a focus group held with CAC members, which includes teachers and youth, to enable researchers to assess the validity of study findings [40]. CAC members will assist with the interpretation of findings in relation to participants’ narratives and validation of study conclusions.

#### Analysis of survey data

Descriptive statistics will be used to assess balance between clusters and to describe schools relative to the required sample size at each timepoint, socio-demographic characteristics, and primary/secondary outcomes. Main analyses will use linear mixed effect models (LMEM) or generalized linear mixed effect models (GLMEM) to assess the intervention effect. LMEM will be used for continuous outcomes that approach normality and GLMEM will be used for binary and other types of outcomes. Normality will be assessed using model residuals and outliers by Cook’s distance, leverage, and residuals. Time in weeks from the beginning of the trial, time in weeks centered at the beginning of the intervention, time in weeks from the beginning of school semesters, and blocks will be specified as fixed effects. The multilevel structure will be defined by assessments within participants as level one, participants as level two, and schools as level three. Schools and participants within schools will be specified as random effects. Main analyses will follow an intention-to-treat approach, with clusters analyzed as per the original treatment assignment. Sensitivity analyses will be performed to assess bias arising from attrition. A significance level of 0.05 will be used in all statistical tests. Analyses will be conducted in SAS v9.4.

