**Fig. 1 Fig1:**
[figure not shown]
SPIRIT flow diagram

The 32-week stepped-wedge cluster-randomized trial will be implemented in three blocks of four schools, each stratified by school type (primary, secondary), such that each block will consist of two schools of each type. The clusters are assembled into three blocks that will crossover from control to intervention condition, with crossover order selected at random. Including the control period, each school will participate across four 8-week periods with crossover from control to intervention condition occurring after each period [20, 21]. Clusters will receive the intervention over 24 weeks, 16 weeks, or 8 weeks depending on their block allocation (Fig. 2).

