### Outcomes

Outcomes will include self-reported stigma-related measures and clinical measures. The primary outcomes are enacted, anticipated, and internalized stigma as measured using the *Adolescents Living with HIV—Stigma Scale* [30]. Secondary outcomes will include courtesy and perceived stigma measured using *Stewart et al.’s 10-item subscale* [31] and the *Brief Stigma by Association Scale* [32]. Secondary clinical outcomes will include HIV testing frequency among sexually active participants; and linkage to care, time to initiation of antiretroviral therapy (ART), ART adherence, and viral suppression, among participants living with HIV. Study outcomes will be assessed by independent research team members at baseline, following each crossover period (i.e., every 8 weeks), and 5-months after completion of the final intervention block.

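### The main model's listed fixed effects contain no intervention term, and read literally they are exactly collinear, so no listed coefficient is the effect the trial was powered for

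*Protocol article*

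**What the plan says.** The Analysis of survey data section states the purpose of the model: "Main analyses will use linear mixed effect models (LMEM) or generalized linear mixed effect models (GLMEM) to assess the intervention effect". It then gives a specific list of fixed effects, starting with "Time in weeks from the beginning of the trial, time in weeks centered at the beginning of the intervention" and closing with "time in weeks from the beginning of school semesters, and blocks will be specified as fixed effects". On the random part it says: "Schools and participants within schools will be specified as random effects". No term for control versus intervention condition appears in either list.

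The Study design section ties crossover to block: "The clusters are assembled into three blocks that will crossover from control to intervention condition, with crossover order selected at random". It adds: "Clusters will receive the intervention over 24 weeks, 16 weeks, or 8 weeks depending on their block allocation". The trial lasts 32 weeks in four 8-week periods. The Outcomes section schedules surveys at baseline, then "following each crossover period (i.e., every 8 weeks), and 5-months after completion of the final intervention block".

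The Power calculation section is built on one step change: 60% to 48%, an absolute difference of 12 points, with 98% power at ICC 0.01, 12 schools and 75 students per school.

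**The concern.** A stepped-wedge analysis estimates its effect from the contrast between control and intervention periods, adjusted for calendar time. That needs a term that changes when a school crosses over. The only listed term that refers to the intervention is centered time. Taken literally, it runs through negative values before crossover and positive values after it along one straight line, so it marks no change at crossover. Once trial time and block are in the model, it also carries no information of its own.

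Two things are at stake. If the list is followed literally, the software must drop a term, and the coefficient printed for centered time is either absent or a difference between blocks. If the analyst instead chooses a workable coding when the fit fails, the primary estimand of a 12-school trial is settled after the data are in.

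**Working it through.** **1. The plan's own power figure.** Inputs from Power calculation: I = 12 schools, T = 4 periods, m = 75 per school per period, 0.60 versus 0.48, ICC 0.01, two-sided 5%. The Hussey-Hughes variance for a 0/1 step with categorical periods is

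v = I·s·(s + T·τ²) / [(I·U − W)·s + (U² + I·T·U − T·W − I·V)·τ²].

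- Total variance 0.54 × 0.46 = 0.2484; τ² = 0.01 × 0.2484 = 0.002484; s = 0.99 × 0.2484 / 75 = 0.003279.
- U = 4(3 + 2 + 1) = 24; W = 0² + 4² + 8² + 12² = 224; V = 4(9 + 4 + 1) = 56.
- Numerator 12 × 0.003279 × 0.013215 = 0.000520. Denominator 64 × 0.003279 + 160 × 0.002484 = 0.6073.
- v = 0.000856, SE = 0.0293, 0.12 / 0.0293 = 4.10, power = Φ(4.10 − 1.96) = 98.4%.

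The stated 98% reproduces, and it belongs to a step indicator.

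**2. Collinearity on the literal reading.** Exposure of 24, 16 or 8 weeks in a 32-week trial gives start weeks 32 − 24 = 8, 32 − 16 = 16 and 32 − 8 = 24. With t for trial time and b2, b3 for membership of the second and third blocks to cross over,

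c = t − 8 − 8·b2 − 16·b3, exactly.

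- The matrix [1, t, c, b2, b3] has rank 4 of 5. With semester time added it has rank 5 of 6. Semester length is not given; 12, 17 and 20 weeks were tried with the same result.
- The result is the same for assessments at weeks 8 to 32, at weeks 0 to 32, and with a late visit placed at an assumed week 54. Irregular survey dates do not help, because c = t minus a block constant at any t. The choice of link function is irrelevant.
- A 0/1 indicator is not a combination of the listed terms: for weeks 0 to 32 (17-week semester assumed), a residual sum of squares of 4.09 out of 14.4 is left unexplained.

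**3. What would be printed.** In the listed order, with the last block as reference, centered time stays in and the second block's term drops out. Blocks 2 and 3 are then separated only by centered time, which differs between them by 8 weeks. Suppose there is no intervention effect, but block 3 happens to lie 6 points above the other two (a hypothetical value). The coefficient is −6 / 8 = −0.75 points per week, which looks like benefit. With blocks listed first, centered time is the term dropped.

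**4. The alternative coding, 0 before crossover.** The listed terms then have full rank (6 of 6 with semester time). Power was computed by generalised least squares with linear trial time and block terms, without semester time, for a true immediate 12-point step. An assessment in the crossover week counts as control.

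| Within-participant correlation | 4 periods | 5 assessments |
|---|---|---|
| 0 | slope 0.00341, SE 0.00264: Φ(1.29 − 1.96) = 25% | slope 0.00455, SE 0.00197: Φ(2.31 − 1.96) = 64% |
| 0.5 (assumed) | SE 0.00187: Φ(1.82 − 1.96) = 45% | SE 0.00139: Φ(3.26 − 1.96) = 90% |

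Slopes are absolute reductions in the proportion per week.

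**5. Secular trend under that coding.** With no intervention effect and a hypothetical 6-point drop in every school after week 8, the fitted slope times 24 weeks is +4.9 points (4 periods) or +2.7 points (5 assessments). The sign is against the intervention. With categorical time the bias is zero.

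**The case against.** The strongest reply is that this is a condensed article. It says that the models assess the intervention effect and that clusters are analyzed by assigned treatment, so a treatment term may have been intended and the sentence may list only the adjustments. That is possible. But the intention-to-treat sentence says how clusters are classified and adds no model term. The article did not leave the specification to another document; it printed a list, and that list does not serve its stated purpose.

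Four stronger readings are tempting, and the documents do not support them.

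- *The effect cannot be estimated on any reading.* The 0-before-crossover coding removes the collinearity. The text does not say it is meant, but does not exclude it.
- *Power collapses to a quarter of what was stated.* The 25% and 64% ignore the participant random effect that the plan specifies. The documents give no correlation. At 0.3 the figures are 34% and 79%; at 0.7 they are 65% and 99%, so with five assessments the loss can vanish. All of them assume an immediate effect.
- *A step term is always better.* Sessions are weekly and exposure varies by block, so a gradual effect is plausible. If 12 points accrue linearly over 24 weeks, a step indicator with categorical time estimates only about −3 points, with 18% to 23% power, against 47% to 72% for the slope model (no participant correlation). This part of the objection stands and shapes the fix.
- *Block terms must go, or the 5-month visit must be left out.* Adding blocks to a step model at 75 per school and 4 periods lowers power only from about 98% to 97%. Once an indicator replaces centered time, the model has full rank with the late visit included.

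**Conclusion.** The specification is wrong as written and should be corrected before any outcome data are analyzed. Two facts rest on the text alone: the list has no control/intervention term, and literally centered time is an exact combination of trial time and block. The second assumes one start week per block, as the Study design section states. On that reading the model yields no intervention effect and can present a block difference as one.

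Under the 0-before-crossover reading the defect is smaller but remains: the model tests a slope while the sample size rests on a step. The shortfall against 98% depends on the assumed within-participant correlation and on the effect being immediate. The bias of about 3 to 5 points depends on a hypothetical trend and shows the exposure; it is not a forecast. The stated 98% is not in dispute for a step model with 75 students per school in each period.

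**What to change.** Replace the fixed-effect sentence so that it:

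1. names a 0/1 intervention indicator (0 before the school crosses over, 1 after) as the primary intervention term, and says how an assessment in the crossover week is coded;
2. models assessment time as a categorical factor in place of linear trial time;
3. defines time since crossover as 0 before crossover and keeps it as a separate pre-specified term for change with exposure. Adding the indicator but leaving literal centered time in place is not enough: that term stays redundant (rank 6 of 7).

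Block effects may be kept or dropped, provided the choice is stated in advance. The 5-month visit stays for the planned sustainability analysis.

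The cost is one paragraph of text and a few degrees of freedom. A single step term can understate an effect that builds gradually, which is why the exposure-time analysis is kept alongside it.

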### Power calculation

Using the power and detectable-difference calculations for stepped-wedge cluster-randomized trials (91) (Stata 14.2), we calculated 98% power to detect a 20% reduction (i.e., an absolute risk difference of 12%) in the proportion of young people reporting a stigma endpoint (i.e., endorsing sufficient elements in the primary stigma measure) given a baseline proportion of 60% experiencing HIV-related stigma, a 5% two-tailed type I error rate, and an intra-cluster correlation coefficient (ICC) of 0.01. There is a lack of published ICC estimates in this setting. Prior work in sub-Saharan Africa and rural Uganda found that 50% of participants experienced stigma in some form [33]. Given our team’s prior experience working among young people in areas recovering from conflict, we have assumed a higher baseline proportion of 60% to have experienced HIV-related stigma. We targeted a total cluster size of 12, with four schools (two primary and two secondary) grouped to crossover from control to intervention at three specified crossover points. We estimate that there will be 150 students enrolled per school across eligible grade levels. Assuming a 50% participation rate after attrition, we estimate that the evaluation will reach 75 students per school for a total sample of *n*=900 who will complete the surveys at the end of the final data collection period﻿ [34].

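### The main model gives each school one constant random effect, so full-cohort standard errors are too small if school levels drift between periods

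*Protocol article*

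**What the plan says.** The Analysis of survey data section of the protocol article describes three levels: "The multilevel structure will be defined by assessments within participants as level one, participants as level two, and schools as level three". It then names the random effects: "Schools and participants within schools will be specified as random effects". No school-by-period effect, random slope or decaying correlation appears.

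The fixed effects begin with "Time in weeks from the beginning of the trial, time in weeks centered at the beginning of the intervention" and go on to weeks since the start of the semester and block. None of these is specific to a school.

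The Power calculation section uses a single ICC of 0.01, gives no between-period correlation, and concedes: "There is a lack of published ICC estimates in this setting". It plans 12 schools in three groups of four, 75 students per school after attrition, a fall from 60% by 12 points, and "a 5% two-tailed type I error rate". It reports 98% power.

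**The concern.** In this design every school moves from control to intervention at one of three crossover points over four 8-week periods, so the effect is estimated largely from change within schools over time. A constant school effect removes stable differences between schools. It does not represent a school whose level shifts from one period to the next for its own reasons. The article gives grounds to expect some of this: its Discussion mentions teacher workload, COVID-19 absence and dropout.

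Because the fixed time terms are shared across schools, they cannot absorb such shifts. The model would treat a shift common to 75 students as 75 independent deviations. At stake is whether the 5% level and the confidence intervals mean what they say for outcomes analysed in the full cohort.

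**Working it through.** **Inputs from the article.** 12 schools, 4 periods, 4 schools crossing at each step, 75 students per school, 60% versus 48%, ICC 0.01, two-sided 5%; HIV prevalence 7.2% in ages 15–24 (Setting and participants).

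**Assumptions, not in the article.** Between-period school correlation c (between-period ICC divided by within-period ICC): 1 means no drift, 0.8 is the main case. ICC 0.05 as an alternative. Within-student correlation r (the share of non-school variance that persists within a student): 0 to 0.5. Categorical periods and an on/off treatment term stand in for the article's continuous week terms.

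**Step 1: reproduce the stated power.** The Hussey–Hughes variance, with treated schools per period of 0, 4, 8 and 12, has
- U = 24, W = 0² + 4² + 8² + 12² = 224, V = 4(3² + 2² + 1²) = 56
- IU − W = 288 − 224 = 64
- U² + ITU − TW − IV = 576 + 1152 − 896 − 672 = 160

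so Var = 12·s·(s + 4t) / (64s + 160t). With total variance 0.54 × 0.46 = 0.2484 (the proportion midway between 60% and 48%):
- t = 0.2484 × ICC × c
- s = 0.2484 × [(1 − ICC)/75 + ICC(1 − c)]
- power = Φ(0.12/SE − 1.96)

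| ICC | c | t | s | SE | Power |
|---|---|---|---|---|---|
| 0.01 | 1 | 0.002484 | 0.003279 | 0.0293 | 98.4% |
| 0.01 | 0.8 | 0.001987 | 0.003776 | 0.0308 | 97.3% |
| 0.05 | 1 | 0.012420 | 0.003146 | 0.0302 | 97.8% |
| 0.05 | 0.8 | 0.009936 | 0.005630 | 0.0396 | 85.7% |

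The first row matches the article's 98%. The stated power therefore corresponds to no drift and 75 students in every school-period. Splitting the 75 over four periods gives only 60%.

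**Step 2: type I error of the stated random effects.** Take total variance as 1, m students per school, g = ICC(1 − c), p = (1 − ICC)r and e = (1 − ICC)(1 − r). For the four period means of a school (J is the all-ones matrix, I the identity):
- true covariance: (ICC·c + p/m)J + (g + e/m)I
- covariance as the stated model sees it: (ICC·c + g/4 + p/m)J + (e/m)I

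The model SE comes from the second matrix; the true SE is the sandwich of the two. With R = true SE / model SE, type I error = 2[1 − Φ(1.96/R)]. At c = 0.8:

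| Students per school | ICC | r | R | Type I error |
|---|---|---|---|---|
| 75 | 0.01 | 0 | 1.063 | 6.5% |
| 75 | 0.01 | 0.5 | 1.134 | 8.4% |
| 75 | 0.05 | 0 | 1.326 | 13.9% |
| 75 | 0.05 | 0.5 | 1.597 | 22.0% |
| 5 | 0.01 | 0.5 | 1.009 | 5.2% |
| 5 | 0.05 | 0.5 | 1.047 | 6.1% |

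Example: 1.96/1.597 = 1.227 and 2(1 − 0.890) = 0.220. With r = 0.7 and 75 students, the figures would be 10.8% (ICC 0.01) and 30.2% (ICC 0.05).

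The 5 students come from 0.072 × 75 = 5.4. Over c = 0.9 to 0.5 at r = 0.5, type I error in that subgroup runs from 5.1% to 7.8%. It reaches 10.0% only at the extreme of r = 0.7, ICC 0.05 and c = 0.5.

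**Step 3: simulation check.** REML fits to a Gaussian outcome, 75 students per school, r = 0.5, 1000 runs per setting (simulation error up to about 1.5 points), z-test:

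| Model and data | ICC 0.01 | ICC 0.05 |
|---|---|---|
| Stated random effects, no drift | 3.9% | 5.8% |
| Stated random effects, c = 0.9 | 7.3% | 13.1% |
| Stated random effects, c = 0.8 | 8.4% | 21.9% |
| Stated random effects, c = 0.5 | 15.6% | 36.2% |
| School-by-period effect added, c = 0.8 | 5.1% | 5.6% |

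The simulation agrees with step 2, and the added term brings the error back close to 5%.

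**The case against.** The strongest reply is that the primary outcomes are hardly touched. Survey design and measurements says that enacted, anticipated and internalized stigma are measured among HIV-positive students. With about 5 of them per school, sampling noise swamps any school drift. This stands, and it limits the point mainly to full-cohort outcomes. It does not remove the point, because the power calculation itself rests on 75 students per school.

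A second reply is that the harm depends on drift, which the article does not estimate, and that at the planned ICC the loss of power is about one percentage point. Both statements are true. But the article also says it has no published ICC to rely on, so 0.01 cannot be counted on to keep the problem small.

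Three stronger readings are tempting, and the article does not support them:
- **That no small-sample correction will be used with 12 schools.** The article is silent. It says only "Analyses will be conducted in SAS v9.4" and "A significance level of 0.05 will be used in all statistical tests". A degrees-of-freedom method is commonly left to the SAP.
- **That using 1.96 in place of a t quantile inflates the error by itself.** The area of t on 10 degrees of freedom beyond ±1.96 is 7.8%, but the simulated z-test without drift gave 3.9% and 5.8%. Nor does a t reference on 10 degrees of freedom cure drift: at ICC 0.05 and c = 0.8 the error is still 14.0%.
- **That the power figure is optimistic whenever the ICC exceeds 0.01.** Without drift, ICC 0.05 costs 0.6 points (98.4% to 97.8%). The fall to about 86% needs both the higher ICC and the drift.

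**Conclusion.** The point holds in a conditional form. The article fixes a covariance structure that leaves out school-by-period variation. If that variation exists, full-cohort analyses understate their standard errors. The understatement is modest at the planned ICC (true SE 6–13% above the model's at c = 0.8) and serious at ICC 0.05 (33–60%). It is slight where only HIV-positive students are analysed.

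The values of c, r and the higher ICC are assumptions. A Gaussian outcome stood in for the binary one in the simulation, and categorical periods replaced the continuous week terms, so the figures show the order of magnitude and are not forecasts for the planned model. Unlike a detail left to the SAP, the random effects are written down, so elaboration alone would not repair this: the stated model has to change.

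**What to change.** In Analysis of survey data, add a random school-by-period effect to the school and participant random effects in both the linear and the generalized linear mixed models. A between-period correlation that decays with time apart is an alternative.

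In Power calculation, state the between-period correlation behind the 98% and show power over a range, for example ICC 0.01 to 0.05 with correlation 0.8 to 1. The degrees-of-freedom method can be named in the SAP.

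The cost is one extra random term in the SAS code and slightly wider intervals at the planned ICC. Where drift is larger the intervals widen more, which is what they should then show. The article says study recruitment is still to begin, so the change can be made before any outcome data exist.

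### Three primary stigma outcomes are each tested at 0.05 with no rule for what counts as success, and the plan does not say whether scores or the powered binary endpoint carry the primary analysis

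*Protocol article*

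**What the plan says.** The Outcomes section states: "The primary outcomes are enacted, anticipated, and internalized stigma as measured using the" adolescent HIV stigma scale. None of the three is marked as leading. Analysis of survey data sets the threshold: "A significance level of 0.05 will be used in all statistical tests".

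The Power calculation section works with one binary quantity, a reduction "in the proportion of young people reporting a stigma endpoint", explained there as "endorsing sufficient elements in the primary stigma measure". It is sized "given a baseline proportion of 60% experiencing HIV-related stigma", with "a 5% two-tailed type I error rate, and an intra-cluster correlation coefficient (ICC) of 0.01", and reports 98% power for a fall of 12 percentage points.

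On the form of the analysis, the survey-data section says "LMEM will be used for continuous outcomes that approach normality", with generalized models for binary and other outcomes, and normality judged from model residuals. The article does not say which of these the three primary outcomes are.

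**The concern.** Planning spends the whole two-sided 5% on one test, while the analysis runs three primary tests at 5% each. The article gives no testing order, no split of alpha and no requirement that all three succeed. A trial with no effect on any of the three then has three chances to produce a significant primary result. At stake is how a report of an effect on one subscale out of three should be read: its false-positive risk would be higher than the 5% used to plan the trial.

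A second gap sits beside this one. The only endpoint with a power statement is a yes/no proportion, but the analysis section allows a continuous score. Until the plan says which is primary, the 98% cannot be attached to any of the three named outcomes with confidence.

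**Working it through.** **Inputs from the protocol article.** Three primary outcomes (Outcomes). 0.05 for every test (Analysis of survey data). Two-tailed 5%, ICC 0.01, 60% falling to 48%, 12 schools crossing over four at a time at three points, 75 students per school (Power calculation). Four 8-week periods (Study design).

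**Assumption.** The correlation ρ between the three test statistics is not given. All three are subscales of one instrument, so it should be positive. I use 0 to 0.9.

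**Step 1: reproduce the stated power.** I use the Hussey–Hughes variance with I = 12 schools and T = 4 periods. Schools spend 3, 2 or 1 periods under intervention, so:

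- U = 4 × (3 + 2 + 1) = 24
- W = 0² + 4² + 8² + 12² = 224
- V = 4 × (9 + 4 + 1) = 56
- IU − W = 288 − 224 = 64
- U² + ITU − TW − IV = 576 + 1152 − 896 − 672 = 160

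The mean proportion is 0.54, so the individual variance is 0.54 × 0.46 = 0.2484. The between-school variance is τ² = (0.01/0.99) × 0.2484 = 0.00251. With 75 students per school per period, s = 0.2484/75 = 0.00331.

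Var = I·s·(s + Tτ²) / (64s + 160τ²) = 0.000865, so SE = 0.0294 and 0.12/0.0294 = 4.08.

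Power = Φ(4.08 − 1.96) = 98.3%. Other conventions for the binomial variance give up to 98.7%. The stated 98% is reproduced, provided 75 students are assessed in every period. Spreading 75 over the four periods (18.75 each) would give about 60%.

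**Step 2: family-wise error of three tests at 0.05 with no true effect.**

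Independent tests: 1 − 0.95³ = 14.3%.

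Equally correlated tests, with c = 1.96:

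1 − ∫ φ(u) [Φ((c − √ρ·u)/√(1−ρ)) − Φ((−c − √ρ·u)/√(1−ρ))]³ du

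| ρ | Each at 0.05 | Each at 0.05/3 |
|---|---|---|
| 0 | 14.3% | 4.9% |
| 0.3 | 13.6% | 4.8% |
| 0.5 | 12.5% | 4.5% |
| 0.7 | 10.9% | 3.9% |
| 0.8 | 9.8% | 3.5% |
| 0.9 | 8.4% | 3.0% |

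With no effect on any outcome, Holm's first step is the 0.05/3 test, so the right-hand column also describes Holm in that case.

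**Step 3: power cost.** The strictest Holm step is 0.05/3 = 0.0167, with critical value 2.394. Power = Φ(4.08 − 2.394) = 95.4%, and up to 96.2% under the other variance conventions.

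**Step 4: how far that cost depends on who is analysed.** Survey design and measurements applies the primary scale to HIV-positive students. Suppose the 7.2% prevalence given for ages 15–24 in Setting and participants applied; this is an assumption, since eligibility starts at age 10.

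- 75 × 0.072 = 5.4 students per school: power about 24% at 0.05 and 13% at 0.0167.
- 150 × 0.072 = 10.8 students per school: power about 41% at 0.05 and 25% at 0.0167.

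These figures only show that the cost in Step 3 is tied to 75 analysable students per school.

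**The case against.** The strongest reply has four parts.

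- **No success rule is stated.** The first objective speaks of assessing the magnitude of change, which is estimation wording. If all three outcomes had to be significant there would be no inflation. This stands as a condition on the result. But the article does not say that all three are required, and it plans explicitly on a type I error rate.
- **Adjustment may sit in an analysis plan that is not shown.** Comparing adjusted p-values with 0.05 would be consistent with the blanket sentence, so that sentence does not strictly forbid adjustment, and silence alone would be no finding. The article is not silent, though. It states a single threshold for every test, and a reader who follows it as written would test each of the three primaries at 0.05.
- **The correlation is unknown.** At 0.8 and above the error is below 10%. A reader might infer that it is at least double the planned 5%; that holds only up to a correlation a little under 0.8.
- **Checking residuals to choose a model family is routine.** A reader might infer that scores will be dichotomised once the data have been seen, or that the residual check feeds the 8–14%. The text says neither. The whole figure comes from three tests, and any effect of the model choice cannot be quantified from the article.

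A reader might also infer that the powered endpoint is none of the three primary outcomes. That is too strong. The power section ties it to the primary stigma measure, which is the scale supplying all three. The text leaves open whether the yes/no cut applies to the whole scale or to each subscale.

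**Conclusion.** The concern holds in a bounded form. With three primary outcomes each tested at 0.05, the family-wise type I error is about 8–14% against the 5% used in planning. This rests on two assumptions: that significance on any one outcome is a primary success, and that the correlation lies between 0.9 and 0. No correlation in that range brings the error back to 5%.

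The unfixed form of the primary analysis is a separate point of clarity with no number attached: the article powers a proportion and permits a score, without saying which one decides. The trial can still be run as designed. Both matters should be settled in the text before outcome data exist.

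**What to change.** 1. Replace the blanket 0.05 sentence with a rule for the primary family: Holm across enacted, anticipated and internalized stigma at family-wise two-sided 0.05. Naming one lead outcome would serve equally.
2. State that secondary outcomes are tested without multiplicity control and read accordingly.
3. State, before data collection, whether the score or the binary endpoint is the primary form of each outcome. If it is binary, define the cut and say whether it applies per subscale. Match the power calculation to that choice. Either form is defensible; a linear model need not be imposed.

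The cost is a few sentences. On the plan's inputs (binary endpoint, 75 students per school) power per outcome at the strictest Holm step falls from about 98% to about 95–96%. If the scale is analysed in HIV-positive students only, the relative loss is much larger, as Step 4 of the working shows, and the power statement should be redone for that population. If the chosen form is the score, the power cost has to be recalculated, because the figures here are for a proportion.
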